**Figure 2 fig2:**
[figure not shown]
Static balance test. **(A)** Protocol for the Romberg test without a foam rubber and for the visual, verbal, lower and upper motor static functional test. **(B)** Protocol for the Romberg test with a foam rubber under the feet. **(C)** Gait model composed by tuberosity of fifth metatarsal (5MTT), posterior surface of calcaneus (CAL), greater trochanter of the femur (GT), lateral condyle of the knee (LC), and lateral malleolus of the ankle (LM).

In addition to balance assessment, the gait of participants will also be measured in a 10 m-long, straight and flat walkway by NedAMH+®/IBV software (v1.1.1, Institute of Biomechanics of Valencia, Spain) which uses two red-light photocells to measure gait speed besides a 3D photogrammetry system with 12 smart-cams (Kinescan®/IBV, version 5.3.0.1, Biomechanics Institute of Valencia, Valencia, Spain), and the dynamometric platform mentioned above. The biomechanical gait model aims to measure movement in the sagittal plane and is made up of 10 landmarks (5 on each leg), located at the anatomical points in Figure 2C. A total of 10 walking repetitions will be analyzed, of which five corresponded to the force data of the right footprint and the other five to the left footprint. Participants will be allowed to walk along the corridor a few times before recording their gait (San Martín Valenzuela et al., 2020a,b). The outcomes from the gait biomechanical assessment are shown in Table 2, and they represent the tertiary outcomes of this study along with those outcomes related to the quality of life, cognitive and mental state, and severity of PD.

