
**Table 2 tab2:** Summary of outcomes, measurement instruments, and assessment times.

Domain / Outcomes	Measurement instrument	Study period			
		Enroll (−t1)	Basal (t0)	Post (t1)	Follow (t2)
Enrollment					
Eligibility screen	Participation criteria	x			
Informed consent	Supplementary material 3	x			
Personal information	SNCI for PD (Supplementary material 4)				
Habits and working life					
Anthropometric data (weigh, height, body mass index, and lower limb length)	Wall stadiometer, TANITA SC-240MA scale, and tape measure	x			
Parkinson’s disease information					
Disease start and initial sign	SNCI for PD	x			
Parkinson’s disease severity	H&Y; UPDRS-III	–	x	x	x
Cognitive and mental status					
General cognitive state	MMP; SCOPA-COG	–	x	x	x
Executive cognitive function	FAB	–	x	x	x
Anxiety	HS for anxiety				
Depression	HS for depression	–	x	x	x
Balance and gait clinical performance					
Balance	MBT; TMT balance	–	x	x	x
Gait	TMT gait	–	x	x	x
Freezing of gait	FOG-Q	–	x	x	x
Quality of life					
Impact on life due COVID pandemic	CPI-Q		x	–	–
Perception of QoL due to Parkinson’s disease	PDQ-39		x	x	x
Confidence on self-balance	ABC scale				
Balance biomechanical performance					
*Static balance: Romberg and Functional test*					
ML and AP OP displacement (mm)	Dynamometric platform	–	x	x	x
Total CoP displacement (mm)		–	x	x	x
CoP displacement angle (°)		–	x	x	x
Mean CoP velocity (ms^−1^)		–	x	x	x
ML and AP CoP dispersion (mm)		–	x	x	x
CoP swept area (mm^2^)		–	x	x	x
*Dynamic balance: stability limits test*					
Reaction time (*s*)	Dynamometric platform	–	x	x	x
Maximum CoP displacement (%)		–	x	x	x
Success (%)		–	x	x	x
Directional control (%)		–	x	x	x
*Dynamic balance: rhythmic and directional control test*					
Directional adjustment (%)	Dynamometric platform	–	x	x	x
Perpendicular adjustment (%)		–	x	x	x
Gait biomechanical performance					
Speed (ms^−1^) and speed variability	3D photogrammetry Dynamometric platform	–	x	x	x
Stride length (m) and time (*s)*		–	x	x	x
Step length (m) and width (*m*)		–	x	x	x
Cadence (steps/min)		–	x	x	x
Double support time (%)		–	x	x	x
Stance and swing phase time (*s*)		–	x	x	x
Maximum ankle dorsiflexion during swing (°)		–	x	x	x
Maximum knee flexion during swing (°)		–	x	x	x
Maximum hip extension during stance (°)		–	x	x	x
Maximum hip flexion during swing (°)		–	x	x	x
Range of motion of lower limb joint (°)		–	x	x	x
CoP medial-lateral displacement (mm)		–	x	x	x
Mediolateral force amplitude (*N*)		–	x	x	x

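### The leg-only gait landmarks cannot give a pelvis-relative hip angle, so two tertiary rows of Table 2 are thigh inclinations under a hip label

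*Protocol article*

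**What the plan says.** Under Section 2.2.3 (Outcomes and participant timeline), the text below Figure 2 sets the purpose of the model: "The biomechanical gait model aims to measure movement in the sagittal plane". It then fixes the number and place of the landmarks: the model "is made up of 10 landmarks (5 on each leg), located at the anatomical points in Figure 2C".

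The Figure 2 legend names the five points per leg. Two are on the foot, at the heel bone and the fifth metatarsal. The remaining three are given as "greater trochanter of the femur (GT), lateral condyle of the knee (LC), and lateral malleolus of the ankle (LM"). The drawing itself is not reproduced in the text at hand, but the legend names every point.

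The gait block of Table 2 lists, at baseline, post-training and follow-up, four peak joint angles: one at the ankle, one at the knee, and two at the hip, "Maximum hip extension during stance" and "Maximum hip flexion during swing". A further row reads "Range of motion of lower limb joint", without naming the joints. The instruments given for the block are 3D photogrammetry and the force platform; the text adds photocells for speed. The article does not define the hip angle. Section 2.2.3 ranks all gait biomechanics as tertiary.

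**The concern.** An anatomical hip angle is the orientation of the thigh relative to the pelvis or, in simpler models, the trunk. The stated markers describe the thigh and everything below it, but neither segment above it. The two hip rows therefore name a joint angle that the stated model cannot supply.

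What the markers can supply is the inclination of the thigh in the laboratory frame. The two quantities differ by the sagittal tilt of the pelvis. In this trial that tilt cannot simply be taken as neutral or fixed. The Introduction counts flexed posture among the features of the disease. Section 2.2.2 describes a home program whose warm-up works on the pelvic and shoulder girdles and on posture, and a standard program that trains the trunk; passive control participants receive neither. If tilt changed between visits, a change in thigh inclination might be reported as a change at the hip joint when the hip had not changed, or a real hip change might be missed.

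**Working it through.** **Inputs.** Five named landmarks per leg and two legs (Figure 2 legend and the text below it); two hip peak rows and one general range-of-motion row (Table 2). The degree values used below are assumptions for illustration; the documents give none.

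**Reproducing the plan's figure.** 5 landmarks × 2 legs = 10, as stated. The list is closed, so none is left over for the pelvis or trunk.

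**What the points define, per leg.**
- Foot: calcaneus to fifth metatarsal.
- Shank: malleolus to knee condyle.
- Thigh: knee condyle to greater trochanter.
- Ankle angle: foot against shank, derivable.
- Knee angle: shank against thigh, derivable.
- Hip angle: thigh against pelvis or trunk. The second segment is not observed.

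**Identifiability.** Write the sagittal marker positions as a function of four angles (thigh, shank, foot, pelvic tilt), with the trochanter taken as the hip centre. The matrix of derivatives has rank 3 of 4, and the pelvic-tilt column is exactly 0. Thigh, shank and foot can be recovered; tilt cannot. The second trochanter does not help: rotating the pelvis by 10° or 20° about the line joining the two trochanters moves both markers by 0.

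**Relation between the two angles.** With flexion and anterior tilt positive:

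hip angle = thigh inclination + pelvic tilt.

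For the peaks, hip flexion = thigh flexion + tilt, and hip extension = thigh extension − tilt.

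**Absolute values.** Assume thigh peaks of 25° flexion and 15° extension:

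| Assumed tilt | Hip flexion | Hip extension | Range |
|---|---|---|---|
| 0° | 25° | 15° | 40° |
| 10° | 25 + 10 = 35° | 15 − 10 = 5° | 40° |
| 20° | 25 + 20 = 45° | 15 − 20 = −5° | 40° |

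**Change between visits.** From the relation, change in thigh inclination = change in hip angle − change in tilt.
- Tilt the same at both visits: its change is 0 and the two changes agree.
- Hip extension fixed at 5°, tilt moving from 10° to 15°: thigh extension moves from 5 + 10 = 15° to 5 + 15 = 20°. The markers show a 5° gain with no change at the hip.
- Thigh extension fixed at 15°, tilt moving from 10° to 5°: hip extension moves from 15 − 10 = 5° to 15 − 5 = 10°. The markers show nothing.

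**Range within a stride.** At constant tilt the range is 25 + 15 = 40° on either definition. If tilt differs between the two peaks by an assumed 2° to 6°, the hip range lies between 40 − 2 = 38° and 40 + 2 = 42°, widening to 40 − 6 = 34° and 40 + 6 = 46°.

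**Reach.** Two of the four peak joint-angle rows, plus any hip part of the range-of-motion row.

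**The case against.** The strongest reply is that the article never says the hip angle is relative to the pelvis. Thigh orientation in the laboratory frame is computable from the trochanter and knee markers, and angle conventions are often left to a fuller document. This stands in part. A reader might infer that no hip-level outcome can be obtained at all; that goes too far, since a thigh angle can. What is unavailable is the joint angle that the row names suggest. The convention might sit elsewhere, but the marker list is given in full here, and no convention can recover a segment that carries no marker.

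A second reply is that the trial analyses effects of time and group (Section 2.4), from which a constant tilt offset cancels. This also stands. A reader might infer a known bias of several degrees in the group comparison. The documents do not support that: they give no tilt value and do not show that tilt changes with training. A biased group contrast would need the average tilt change to differ between groups. The content of the programs makes that possible, not established.

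Third, the range-of-motion row does not name the hip, and a range is less exposed than a peak. Both points are correct.

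Fourth, the protocol states no hypothesis about hip mobility, so it cannot be said that the authors plan such a claim. That is fair. The risk lies in how a row labelled as a hip angle would be read.

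**Conclusion.** The point holds in limited form. The stated model cannot yield a pelvis- or trunk-relative hip angle, and this follows from the marker list alone. That the reported values would be thigh inclinations is an inference, because the angle is undefined, but it is the only sagittal hip-level angle these markers allow.

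The consequence is one of labelling and interpretation in two tertiary rows, with a lesser effect on any hip range. The size of any misreading equals the change in tilt, which is not measured; the degrees shown above are illustrative.

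A reader might infer wider damage to the trial. There is none from this source: centre-of-pressure sway area, the sample size, and the knee, ankle, spatiotemporal and force outcomes do not depend on a pelvic landmark.

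**What to change.** In Table 2, rename the two hip rows as maximum sagittal thigh extension and maximum sagittal thigh flexion relative to vertical. If the range-of-motion row is meant to include the hip, call that part thigh range. State the reference direction once in Section 2.2.3, and draw no hip-joint conclusion from these variables in the report.

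The cost is wording and a narrower claim. No new data are needed, and the definition is the same for every participant and visit.

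Adding pelvic markers part-way through is not advised. Enrolment began in 2021 (Sections 2.2.1 and 2.2.4), so hip angles would exist only for a late, non-random subset measured with a different model from the earlier participants.

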#### Sample size and recruitment

2.2.4.

The software G*Power v.3.1 (Faul et al., 2007) has been used to determine the necessary sample size to detect a change in the primary outcome CoP sway area and differences between the groups (EG, PCG, ACG), with a small-medium effect (*f* = 0.15), a statistical significance of 5% at the two-tailed level, and a power of 95%. As a result of the above, 93 people diagnosed with PD will be recruited. If 20% of possible dropouts are also considered during the study, the initial recruitment should be 112 people. The sampling process will consist in the consecutive non-probabilistic method, in which the selection of individuals is carried out based on the fulfillment of participation criteria. The recruitment of participants began on 1 July 2021 and we estimate its completion on 31 July 2023. The participant recruitment procedure consists of three steps. First, the neurorehabilitation center has selected the possible candidates for the study based on personal and clinical characteristics, asks them by email the authorization to send information about the study, and contacted them using their telephone number. Then, the principal investigators called potential candidates to resolve possible doubts and confirm their participation. Finally, a physiotherapist will assess the selection criteria for all the volunteers and will provide informed consent for their signatures. The recruitment process will be repeated to complete the number of participants estimated for the study, extending participation to a new clinical center or public hospital if necessary.

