**Methods:**

The initial recruitment was estimated at 112 people with idiopathic PD. Two-thirds of the participants will be randomized to one of the two groups to make the crossover. In contrast, the other third will do a face-to-face group program only. The balanceHOME protocol consists of challenging balance exercises incorporated into functional daily tasks, developed in-home and conducted two times per week for 60-min over an 8-weeks period. The primary strategy will consist of splitting functional tasks of daily life into static and dynamic balance components, besides standardized facilitate and disturbing strategies to execution of each exercise. Biomechanics and clinical performance of balance and gait, perception of quality of life, cognitive and mental functioning, and severity of PD will be measured at baseline (T0), post-8 weeks training (T1), and follow-up (T2).

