Balance alterations in PD are usually assessed in a single task. The most common tests are based on static and dynamic balance, where the patient controls the CoP in a static position (e.g., standing) (Negrini et al., 2017; Giardini et al., 2018; Soke et al., 2019) or during motion in direction to the different LoS (Kara et al., 2012; Carpinella et al., 2017; Soke et al., 2019). To this assessment methodology, it is common to add the blockade of the different systems that participate in balance regulation, either by closing the eyes or placing foam under the feet. Similarly, standard balance physiotherapy is carried out in isolated environments with exercises focused on single tasks or similar scenarios to those of the evaluation (Giardini et al., 2018). Conversely, daily activities are developed in highly challenging environments, which have been addressed in previous publications with Wii balance games (Yen et al., 2011; Zalecki et al., 2013; Carpinella et al., 2017; Negrini et al., 2017; Feng et al., 2019; Yuan et al., 2020), dual-task exercises within daily activities (Conradsson et al., 2015; Wong-Yu and Mak, 2015a, 2015b; Atterbury and Welman, 2017; Perumal et al., 2017; Santos et al., 2017; Wallén et al., 2018; Leavy et al., 2020), and single daily activities training (Smania et al., 2010; Kara et al., 2012b) including postural transferences (Millage et al., 2017; Soke et al., 2019). Although functional balance training (FBT) is included in the latest protocols, which consists of daily activities with feasible settings for older adults with PD, there are several methodological issues that have not yet been considered. One of these is the assessment methodology of the previous studies and the objectivity of the measurements, using in most cases, scales, and clinical tests only (Conradsson et al., 2015; Wong-Yu and Mak, 2015a,b; Atterbury and Welman, 2017; Perumal et al., 2017; Santos et al., 2017; Wallén et al., 2018; Leavy et al., 2020) instead of integrating biomechanical parameters of balance in different measurement conditions with a follow-up period after finishing the studied intervention (Kara et al., 2012b; Conradsson et al., 2015; Atterbury and Welman, 2017; Perumal et al., 2017; Santos et al., 2017; Soke et al., 2019; Leavy et al., 2020). Furthermore, the authors who inform significant improvement in balance biomechanics (Kara et al., 2012; Santos et al., 2017; Soke et al., 2019) do so in patients with normal cognition status and use habitual locations like a physiotherapy gym or hospital facilities. To respond to the challenges that emerged since the COVID-19 pandemic, such as the demand for rehabilitation programs that can be followed from home, the effect of domiciliary FBT and the long-term impact with adequate follow-up need still be determined, as well as the effects in people with PD in advanced stages where cognition is altered. For the foregoing, the aims of this study are (1) to quantify the effects achieved by domiciliary FBT on the biomechanics of balance, gait, perception of quality of life, cognitive and mental performance, and severity of PD in participants with and without cognitive impairment and (2) to compare them with the effects of a passive-control period and a conventional face-to-face physiotherapy program for PD. We hypothesized that balance home training based on functional exercises has a greater effect than the traditional physiotherapy group. If this hypothesis is confirmed, it will open the possibility of new rehabilitation strategies according to changes in post-pandemic therapeutic approaches, reducing morbidity, and saving costs to the healthcare system.

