### Data collection, management, and statistical analysis

2.4.

Both evaluators (physiotherapist and neuropsychologist) will be responsible for exporting and filling in a database with variables from the scales and tests mentioned in Table 2 according to the code assigned to each patient to ensure his or her anonymity. To protect confidentiality during the study, the personal information of participants will be located separately from the main dataset on a local computer. The raw dataset will be maintained for 10 years after the completion of the trial with indefinite restricted access due to sensitive data. After the publication of the results trial, a fully anonymized patient-level dataset will be made publicly available on the registration trial website (clinicaltrials.gov). For participation in this study, no participant will receive any kind of incentives or compensation.

All analyses will be evaluated by intention-to-treat principles in terms of assignment to treatment and used a level of significance of 0.05. There are no interim analyses planned for this study. We will use the statistical software SPSS Statistics version 24.0 (IBM Corporation) for all the statistical analyses. Categorical variables were presented using frequency and percentage, and continuous variables as mean with standard deviation if they follow a normal distribution. To test for possible carryover effects of the experimental group, the sum of the values measured in the two periods for each subject will be calculated and compared across the two randomized groups (EG and PCG) using a test for independent samples (Serrao et al., 2019). There should be no difference if there is no sequence (balanceHOME program—usual daily activity or usual daily activity—balanceHOME program) effect.

To answer to the main aim of the study, a two-factor mixed multivariate analysis of variance (MANOVA) test was conducted to analyze the effects of within-subject factors (assessment times) and the between-subject factor (group) on the outcomes registered. The Bonferroni adjustment was used for *post-hoc* comparisons, and differences were declared statistically significant if the value of *p* was less than 0.05. Differences between groups for demographic outcomes were verified with a univariate analysis of variance (ANOVA) between-subjects test. Furthermore, to test for sex differences between groups, a chi-square analysis was used (San Martín Valenzuela et al., 2020b).

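### The stated 95% power belongs to a three-group comparison and does not carry over to the one stated hypothesis, balanceHOME versus group physiotherapy

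*Protocol article*

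**What the plan says.** Section 2.2.4 (Sample size and recruitment) gives one calculation, whose purpose is to "detect a change in the primary outcome CoP sway area and differences between the groups (EG, PCG, ACG), with a small-medium effect". The inputs are Cohen's f of 0.15, a two-sided alpha of 5% and 95% power. The result is that "93 people diagnosed with PD will be recruited", raised to 112 for dropout. The G*Power test family, the number of measurements and the within-person correlation are not given.

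The Introduction has one sentence worded as a hypothesis: "balance home training based on functional exercises has a greater effect than the traditional physiotherapy group". That is EG versus ACG. The second aim, just before it, names both the passive-control period and conventional physiotherapy as comparators.

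Section 2.4 answers the main aim with a time-by-group mixed MANOVA. On the pairwise step it says "The Bonferroni adjustment was used for" such follow-up comparisons. No separate EG-ACG test is named.

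On allocation, the abstract says: "Two-thirds of the participants will be randomized to one of the two groups to make the crossover". Sections 2.1 and 2.3 confirm that only EG and PCG are randomized, 1:1. ACG consists of people who already attend the group programme.

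**The concern.** Cohen's f over three groups measures the total spread of the three group effects. It does not say how far apart any two groups are. If the passive group is furthest from balanceHOME, most of that spread comes from EG versus PCG, and EG versus ACG holds only part of it. That part is then tested at a smaller alpha, because the post-hoc step is Bonferroni-adjusted.

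A reader who sees 95% power beside a hypothesis about home versus group training may take the figure as the chance of confirming that hypothesis. If the EG-ACG test then fails, the same reader may take the failure as evidence that the two programmes do equally well. The concern does not depend on whether 93 is the right number for the omnibus test. It remains if the 95% is granted in full.

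**Working it through.** **Inputs from the article.** f = 0.15, alpha 5% two-tailed, power 95%, N = 93, dropout 20%, 112 recruited (2.2.4). About one third of participants per group (abstract, 2.3), so 31 each. Three visits per phase, T0, T1 and T2 (2.2.3).

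**Assumptions, not in the article.** Bonferroni over three group pairs, so 0.05/3 per pair. The ACG effect as a fraction of EG's, with PCG at zero. The time profile of the effect.

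**Step 1: the plan's own figure.** For a group-by-time interaction, lambda = f²·N·m/(1 − rho), with df (k − 1)(m − 1) and (N − k)(m − 1), where k is the number of groups and m the number of measurements.
- k = 3, m = 6, rho = 0.5: lambda = 0.0225 × 93 × 6/0.5 = 25.11, power 95.2%. N = 93 is returned exactly.
- k = 3, m = 3, rho = 0.5: lambda = 0.0225 × 93 × 3/0.5 = 12.56, power 81%. N = 141 would be needed.
- k = 3, m = 3: N = 93 is returned at rho of about 0.68.
- Dropout: 93 × 1.2 = 111.6, so 112.

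The 93 can therefore be reached as a three-group test, but the article does not fix which version was used.

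**Step 2: grant the omnibus its 95%.** For three groups and three visits (df 4 and 180), 95% power needs lambda = 19.07.

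**Step 3: the share that reaches EG-ACG.**
- Group share = [(EG − ACG)²/2] / SS of the group effects. With effects 1 : 0.5 : 0 for EG : ACG : PCG, SS = 0.5 and the share is 0.125/0.5 = 0.25. With 1 : 0 : 0, it is 0.5/0.667 = 0.75. With ACG at 75% or 25% of EG, SS = 0.542 and the shares are 0.031/0.542 = 0.058 and 0.281/0.542 = 0.519.
- Time share in the T0-T1 contrast = 0.75 if the effect is fully kept or fully lost at T2, and 1.0 if it is half kept.

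The noncentrality of the t test is the square root of 19.07 × group share × time share, with 90 error df.

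| ACG effect as share of EG's | Group share | Noncentrality | EG-ACG power at 0.05/3 |
|---|---|---|---|
| 75% | 0.058 | 0.91-1.05 | 7-9% |
| 50% | 0.25 | 1.89-2.18 | 30-40% |
| 25% | 0.519 | 2.73-3.15 | 61-76% |
| 0% (same as PCG) | 0.75 | 3.28-3.78 | 80-91% |

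With ACG below PCG by 25% of EG's effect, the share is 0.893 and power is 87-95%. With ACG as far below PCG as EG is above it, the share is 1.0 and power is 91-97%.

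**Step 4: the other pair.** In the half-effect case, EG-PCG has share 0.5/0.5 = 1.0, noncentrality 3.78-4.37 and power 91-97% at 0.05/3. The omnibus power comes mainly from the passive comparison.

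**Step 5: sensitivity of the half-effect case.** With f = 0.15 held fixed, three visits and rho = 0.68, power is 31-42%. At rho = 0.5 it is 19-26%. If PCG's later balanceHOME period were pooled with EG's (62 versus 31, treated as independent, rho = 0.68), it would be 42-55%. Across all variants tried it is about 17-55%.

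**Step 6: closed test.** A three-group test of T0-T1 change at 5% comes first. Each pair is tested at 5% unadjusted only if that is significant. Joint EG-ACG power is about 46-58% in the half-effect case and about 88-95% in the zero-effect case.

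**The case against.** The sizing matches the stated main analysis. Section 2.4 uses a time-by-group test for the main aim, and the second aim includes the passive comparator. The article nowhere attaches the 95% to EG-ACG and plans no equivalence claim. All of this stands: the omnibus sizing is relevant, and misreading is a risk, not something the article does.

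That the calculation is omnibus is inferred. Other test families give about 93 at other correlations, for example 94 for a two-group, three-visit interaction at rho = 0.6. This also stands. It is why the working grants the 95% and does not dispute it.

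The ACG effect is unknown, and f = 0.15 is a planning value. The Discussion cites improvements in sway area of 36.42% and 42%, but without an SD these cannot be turned into an f. Actual power could be higher or lower than the table. A reader might infer that EG-ACG power is 30-40%. The article does not support any single figure, only a range conditional on the ACG effect.

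A reader might also infer that 95% is reached only if ACG mirrors EG on the far side of PCG. That is too strong: the upper end reaches 95% with ACG only 25% of EG's effect below PCG.

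The crossover might add data, since PCG later receives balanceHOME. The article does not say that period will be pooled for this contrast, and pooling would reach only 42-55% in the half-effect case.

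Finally, Bonferroni is a valid procedure, so replacing it is a gain in efficiency and not the correction of an error. Because ACG is not randomized, more power would not make that contrast a randomized one.

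**Conclusion.** The point holds as a mismatch between what was powered and what was hypothesized. The 95% is stated for three groups, while the hypothesis is one pair, reached through an adjusted post-hoc test. With the omnibus 95% granted, EG-ACG power for T0-T1 change runs from 7-9% (ACG at 75% of EG's effect) to 80-91% (ACG no better than PCG), and it approaches 95% only if ACG does worse than no treatment. Section 2.2.2 gives the ACG programme the same frequency and session length as balanceHOME and lists balance among its objectives, so the zero-effect case is the optimistic end.

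The figures rest on equal groups of 31, three visits, three Bonferroni pairs and assumed ACG effects. Counting time pairs in the adjustment would lower them. A reader might infer that N = 93 is wrong or that the trial is underpowered overall. The article does not show that: 93 can be reproduced, and in the half-effect case the randomized EG-PCG contrast keeps about 91-97%.

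**What to change.** **Section 2.2.4.** State that f = 0.15 and 95% refer to the three-group test, and name the G*Power test, the number of measurements and the correlation. For EG-ACG at N = 93, with the alpha that will be used, print either power across a range of ACG effects or the detectable difference in T0-T1 change of CoP sway area.

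**Section 2.4.** For T0-T1 change in CoP sway area, replace the three-pair Bonferroni step with a closed test: the three-group test on that same endpoint at 5%, then, only if it is significant, each pair at 5% unadjusted. With three groups this controls the family-wise error.

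**Reporting.** Give EG-ACG with its confidence interval, note that this comparison is not randomized, and state that a non-significant result is not evidence of equivalence.

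**Cost.** Wording only, with no extra participants. The printed power for the hypothesis will look less favourable. Pairwise claims will require a significant three-group test, which is a small loss. The closed test does not bring the half-effect case near 95%. Reaching that at 0.05/3 would take about 104-138 per group (three visits, rho 0.68), so the gap is better disclosed than presented as solved.
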